### Sampling aspects

The target population of the HE intervention are unemployed people registered at public employment centres for less than 12 months (including first-job seekers). Random recruitment of participants (for both arms of the study) occurs in two employment centres (from different geographical regions), with match-to-case allocation in arms according to gender, age groups (18–24, 25–44, and 45–65 years old) and educational level (9 to 12, and more than 12 years of completed school – higher education). The full list of the two public employment centres users (with inclusion criteria) will be stratified by gender, age groups and educational level. In each combined stratum, random allocation will be done to each participant who accepts to participate.

Inclusion criteria: unemployed users from public employment centres, 18 to 65 years old, both genders, having at least nine years of formal/public education and being registered in the selected public employment centres at the moment of recruitment.

Exclusion criteria: public employment centres’ unemployed users already attending, at the moment of the recruitment, other public employment centre’s courses, or users with a diagnosed mental or physical severe or incapacitating disease or disability.

Two public employment centres/delegations from two Portuguese regions will be selected (intentional sampling) and invited to participate in the project. The involved public employment centres/delegations differ in terms of size (big dimension vs. small dimension) and type of region (rural population vs. urban population). In each centre/delegation, participants are randomly selected from the full database of users. Allocation to arms is done also in a random way, though following gender, age and educational level strata inter-arms matching.

In each of these settings, the initial (at baseline) users sample size will be of 50 participants with 50 other participants as controls. Previewing a dropout rate of 30% till the end of the project, we estimate to have a final users’ sample size of 35 participants in each of the arms, in each employment centre (70 participants per arm, in total). With this sample size, we expect to have 80% power to detect an effect size of 0,48 in mean scores of mental health literacy, psychological well-being, satisfaction with life and resilience [45].

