### Variables in study

Data collection for the controlled community sample will be done for both arms of the trial on three different moments: before the intervention (at baseline), immediately after its ending and three months later.

The indicators for the intervention effectiveness will be: mental health literacy, mental health related personal and perceived stigma, psychological well-being (depression and anxiety), satisfaction with life and resilience. Secondary outcomes include opinions and satisfaction with intervention by intervened unemployed, rate of participation and completion of the intervention. The socio-demographic variables that will be used to characterize the sample and for adjusting outcomes assessment include: age, gender, educational level, previous professional activities, having or not dependent relatives (children, dependent elderly or other relatives to care) and household overall financial comfort.

All questionnaires measuring/assessing constructs (i.e., latent variables) were selected on basis of their psychometric qualities (e.g., internal and temporal reliability, validity) when applied to adult Portuguese general populations. Table 1 provides an overview of the validated instruments that will be included in the effectiveness assessment. Taking into consideration the time usually reported for filling in each of the selected instruments, it is estimated that the total time for filling the complete battery of questionnaires is around 20 min. We will run a pilot test with at least 10 unemployed persons to assess the burden of the questionnaires.

**Table 1 Tab1:** Instruments used in the effectiveness assessment

Assessed constructs	Questionnaire / measure scale	Description
Mental health literacy	Modified/shortened versions of the following instruments:	The DSS is designed to measure stigma associated with depression. It has two subscales which measure two different types of stigma: personal and perceived. Responses to each item are measured on a five-point scale (ranging from zero ‘strongly disagree’ to four ‘strongly agree’). Higher scores indicate higher levels of depression stigma.
	• Depression Stigma Scale (DSS)	
	• Depression Literacy Questionnaire (D-Lit)	

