### Data analysis

Statistical analysis will be carried out using IBM/SPSS 21.0 (or a more updated version, at the moment of the analysis) and R packages. For all tests, the level of statistical significance will be set as α = .05.

For the effectiveness assessment, socio-demographic and outcome variables will be described for each moment of observation. Two strategies of data analysis will be done: (1) intention-to-treat (ITT), as a primary analysis, and; (2) per-protocol, as a supportive analysis. The ITT analysis (treatment as assigned approach), will consider all participants randomly allocated to each arm of the study at baseline with a last observation carried forward imputation for those who did not undergo the final evaluation. The per-protocol analysis (treatment as received approach), will include only the subset of the ITT sample who will completed the evaluations without any major protocol violations. When describing differences between intervention and control group, results from both types of analysis will be reported; for effect size assessment, only per-protocol approach results will be reported, in order to have an estimation of the impact of the treatment as received.

Univariate description of variables will be summarized by central tendency measures (means and medians, according to the normality of their distributions) and respective dispersion measures (standard deviation and range). Normality of data will be assessed through the analysis of kurtosis and skewness.

Association between nominal variables will be assessed through chi-square test (with Yates adjustment, when necessary). Continued variables will be compared (between arms, at the same momentum) by independent samples t-student test or by its non-parametric equivalent (Mann-Whitney test), when adequate.

Effect of the intervention will be studied by linear or logistic regression analysis (according to the nature of the dependent variable), having as dependent variables test-retest variations and adjusting for conceptually (and statistically) relevant variables. Model assumptions will be tested by analysis of residuals and influence diagnostics through Cook’s distance. Cohen’s d coefficient and odds ratio will be used for assessing the size of the intervention effect, when significant.

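### The effect regression may choose its covariates from the trial data and does not guarantee that the factors balanced at allocation, centre included, stay in the model.

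*Protocol article*

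**What the plan says.** **Allocation (Protocol article, Sampling aspects).** Eligible users are stratified by gender, three age groups and two education levels, and participants are randomised within each combined stratum: "Allocation to arms is done also in a random way, though following gender, age and educational level strata inter-arms matching". The two centres are picked on purpose to differ in size and in rural or urban setting. Numbers are fixed within each: "In each of these settings, the initial (at baseline) users sample size will be of 50 participants with 50 other participants as controls". The arms are therefore balanced on the three named factors and, through the per-centre quota, on centre.

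**Adjustment variables (Variables in study).** The socio-demographic variables for adjusting the outcome analysis are age, gender and educational level, then "previous professional activities, having or not dependent relatives", then household financial comfort. The list is introduced as an inclusion, so it is open. Centre is not named.

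**Analysis (Data analysis).** Arms are compared at each time point by a t-test or Mann-Whitney test. The effect of the intervention is assigned to a linear or logistic regression of changes between measurements, "adjusting for conceptually (and statistically) relevant variables". No covariate set is fixed.

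**The concern.** Factors used to balance the arms belong in the model that estimates the effect. Balancing removes their contribution from the chance difference between arms. A model that leaves them out still counts that contribution as noise, so its standard error is too large, its test is conservative and precision already paid for is lost.

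The wording here allows that to happen. Gender, age and education are candidates, but nothing says they stay if they look unimportant in the data. Centre is not mentioned as a covariate, although the contrast between rural and urban settings is part of the first specific objective and the centres were chosen to differ.

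Letting statistical relevance in the trial data influence the covariates also means that the model is not settled before the results are seen. Two competent analysts could follow the sentence and report different estimates, and the model could differ from one outcome to the next.

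**Working it through.** **1. The plan's own figure.** Inputs from Sampling aspects: "we expect to have 80% power to detect an effect size of 0,48 in mean scores"; 100 per arm at baseline; "Previewing a dropout rate of 30% till the end of the project"; hence 70 per arm at the end. From Data analysis: "For all tests, the level of statistical significance will be set as α = .05" (taken as two-sided).
- Completers: 100 × (1 − 0.30) = 70 per arm.
- Standardised signal: 0.48 × √(70/2) = 2.84.
- Power: Φ(2.84 − 1.96) = 81.1%; with the t distribution, 80.5%.

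The stated 80% reproduces.

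**2. What is assumed.** Let R² be the share of outcome variance explained by centre, gender, age group and education together. The article does not give it, so a range of 0.05 to 0.30 is used.

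**3. Outer bound: no balancing factor in the model against all four.** With balanced strata the true standard error is √(1 − R²) times the one an unadjusted analysis uses. At 70 per arm:
- type I error, none: 2 × [1 − Φ(1.96/√(1 − R²))]
- power, none: Φ((2.84 − 1.96)/√(1 − R²))
- power, all four: Φ(2.84/√(1 − R²) − 1.96)

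| R² (assumed) | Type I error, none | Power, none | Power, all four |
|---|---|---|---|
| 0.05 | 4.4% | 81.7% | 83.0% |
| 0.10 | 3.9% | 82.3% | 84.9% |
| 0.20 | 2.8% | 83.7% | 88.8% |
| 0.30 | 1.9% | 85.3% | 92.4% |

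This describes a comparison with no adjustment at all. The planned regression can adjust, so its loss should lie inside these gaps: 1.3 points at R² = 0.05 and 2.6 at 0.10.

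**4. The regression itself, by simulation.** 140 completers; 24 strata (2 centres × 2 × 3 × 2); balanced allocation; one continuous outcome; no baseline score in the model. Centre carried the largest weight, 60% of the explained variance: 1/(1 + 0.25 + 0.167 + 0.25). Data selection meant keeping those of the six listed variables with p < 0.05 against the outcome, with centre not a candidate. There were 3,000 runs under no effect and 2,000 under 0.48.

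| | Type I error at R² = 0.10 / 0.20 / 0.30 | Power at R² = 0.20 |
|---|---|---|
| t-test | 3.7 / 3.1 / 1.8% | 82.8% |
| Gender, age, education; no centre | 4.2 / 3.8 / 2.8% | 84.9% |
| Covariates selected by p-value | 4.1 / 3.7 / 2.7% | 84.6% |
| All four factors | 4.6 / 5.2 / 4.7% | 88.3% |
| Smallest p over all 2⁶ = 64 subsets of the list | 5.6 / 5.2 / 3.9% | not run |

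Simulation error (95%) is about ±0.8 points for type I error near 5% and ±1.6 for power near 85%.

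**5. Cross-check of the no-centre row at R² = 0.20.** The model leaves 1 − 0.4 × 0.20 = 0.92 of the variance as residual, while the true value is 0.80. Power = Φ((2.84 − 1.96 × √0.92)/√0.80) = 85.8%, against 88.8% with centre: a loss of about 3 points, in line with the simulation.

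**6. At the full randomised number.** The primary intention-to-treat analysis keeps all 100 per arm, with the last observation carried forward. The signal becomes 0.48 × √50 = 3.39. The same formulas at R² = 0.20 give 95.5% without centre and 96.7% with it, before any dilution from carrying observations forward. The loss is then about 1 point.

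**The case against.** The case against has several sound parts.

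- **The two-sample tests are not the effect analysis.** A reader might infer that the effect will be tested while ignoring every stratum, and so take the type I errors of 3.9% and 2.8% (R² of 0.10 and 0.20) as those of the trial. The article does not support this: it assigns the effect to the adjusted regression.
- **Centre is not excluded.** A reader might infer that it is, from its absence in the list. But that list is open and covers socio-demographic variables, and centre could enter the model on conceptual grounds. It is unnamed, no more.
- **Selection barely affects false positives.** A reader might infer from 64 possible models that the error rate is inflated. Even the smallest p-value over all 64 gave 3.9% to 5.6%, and ordinary selection stayed below 5%.
- **R² may be small.** The regression models changes. Stable differences in level between centres or groups cancel in a change score, so R² for change may be well below R² for level. The article gives neither.
- **Detail may sit in a separate analysis plan.** The exact model is often fixed there, and this sentence names no threshold or stepwise procedure.

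The first four points stand and limit the size of the problem. The last stands only in part: the article does more than leave the covariates open. It makes statistical relevance one of the grounds for adjustment and gives no assurance that the balancing factors are kept.

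**Conclusion.** The point holds as one of efficiency and pre-specification. The design balances on four factors; the analysis sentence guarantees none of them in the model and lets the data influence the choice.

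At 70 completers per arm and an assumed R² of 0.20, with centre the strongest factor, the regression loses between 3 and 4 points of power: about 85% against 88%. At R² of 0.10 or less the loss is at most about 1 to 3 points, and it shrinks further at 100 per arm or if change scores absorb level differences. Every variant examined stays above the planned 80%, so the stated power is not undermined. The inference errs towards caution, so there is no ground for alleging inflated false positives.

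These figures are for a linear model in which balance is preserved. Effect sizes are to be reported from the per-protocol subset only, where randomised balance is not assured; a fixed adjustment for centre and strata has added value there. The change is worth making because it is almost free, not because the trial's validity is at risk.

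**What to change.** In Data analysis, delete the bracketed reference to statistical relevance and add one statement: every effect regression includes arm, the baseline score of the outcome, centre, gender, age group (three levels) and education (two levels), whatever their significance. Use the remaining socio-demographic variables (previous occupation, dependants, financial comfort) only in a named sensitivity model. State that the regression is the effect analysis and that the t-test and Mann-Whitney comparisons are descriptive.

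Cost: besides arm, the set uses 1 + 1 + 1 + 2 + 1 = 6 degrees of freedom, out of 140 to 200 participants. No further recruitment or measurement is needed, since all these variables are already collected or known at allocation.

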### Ethics

This intervention protocol follows the code of ethics of the Declaration of Helsinki [52]. All participants will be asked to sign an informed consent, with detailed information concerning the goals and procedures of the project, as well as with regard to their full right to refuse or quit their participation at any time. The written informed consent will be signed before the first intervention session.

If the intervention proves to be effective, participants enrolled in the control arm will be invited to benefit from it as well. This research protocol was approved by the Portuguese Protection Data Authority (CNPD). Ethics approval was obtained from the Ethical Committee of Academic Centre of Medicine of Lisbon (University of Lisbon).

## Discussion

In a context of adverse economic climate, vulnerable groups experiencing unemployment have an increased risk of suffering from mood disorders and psychological distress [5, 53, 54]. This paper describes a community-based randomized field study protocol for assessing the effectiveness of a psychological well-being protection and promotion intervention, aiming to build capacity and reduce inequalities within the context of unemployment. This intervention is foreseen as strategic due to its applicability to different community settings and targeted populations. Moreover, the intervention has also a component of socio-cognitive skills development and training for an adequate recognition of psychological suffering and referral to primary healthcare and mental health services.

A main challenge of the field experiment concerns some fundamental characteristics of the intervention, namely in terms of format and duration. The intervention is currently planned to follow a short-term group format, maximizing its potential to be adopted, replicated and sustained in different settings (in both public and private sectors). Another difficulty relates to the fact that the population that may benefit from the intervention is highly heterogeneous, namely regarding financial, sociocultural backgrounds and level of psychological suffering. Therefore, the added-value of the intervention for participants will vary substantially and the overall trial results will need to be stratified by individuals’ characteristics.

Considering the timeframe of the EEA Grants 2009–2014 that financially supported this project (see acknowledgements/funding section), the final evaluation of the intervention will be done three months after its ending. This is a limitation of this study protocol because three months might be a narrow time frame for detecting mental health promotion effects and, on the other hand, possible intervention-related changes can be temporary and not sustainable. Nevertheless, if the intervention shows positive results at the last observation moment, the project team will apply for new funding opportunities to follow the recruited cohort (within this trial) for a longer period.

The external validity of the study will also require replication with larger numbers of participants. The expected results of the study, together with the fact that the involved partners include multilevel and intersectoral stakeholders, in the areas of unemployment, temporary employment, social security, local authorities, health services and entrepreneurial activities, will be instrumental to inform decision makers.

This project is embedded in the strengthening of the bilateral relations between Portugal and EEA Grants’ Donor States (Norway, Iceland and Lichtenstein), namely by sharing scientific knowledge about mental health promotion of vulnerable groups such as those unemployed. The tangible joint results that we hope to reach through this opportunity of cooperation will reinforce the political, professional and human ties between these countries.

## Abbreviations

A-Lit: Anxiety Literacy Questionnaire
BSI: Brief Symptom Inventory
CD-RISC: Connor-Davidson Resilience Scale
CNPD: Portuguese Protection Data Authority
D-Lit: Depression Literacy Questionnaire
DSS: Depression Stigma Scale
EEA Grants: European Economic Area Grants
GHQ: General Health Questionnaire
HE: Healthy Employment
ITT: Intention-to-treat
RE-AIM: Reach, Effectiveness, Adoption, Implementation and Maintenance
SWLS: The Satisfaction with Life Scale
